##### For those randomised to the interventional arm

The nose and throat swab in viral transport medium will be analysed promptly on the FilmArray respiratory panel 2 as per training delivered by the apparatus manufacturer, used as a POCT. FilmArray machines will be located in the clinical areas for this purpose. Test results are generated in around 45 min. Where lower respiratory tract samples are also obtained, these will also be tested on the FilmArray in parallel with the nose and throat swab or sequentially.

The results of the test will be documented in the patient’s case notes and a member of the clinical team responsible for the patient will be directly informed. The participant or consultee will also be informed of the result where appropriate. The infection prevention and control team will be informed of the result within 4 hours of testing. In the event of influenza A or B being detected, clinical teams will be encouraged to offer treatment with NAIs as per national guidelines. It is known that the sensitivity of virus detection may be greater with lower respiratory tract samples versus upper tract samples in certain patients. Therefore, in patient where lower respiratory tract samples are obtained in addition to the upper respiratory tract samples, if either of the swabs are positive they will treated as infected and be reported to the clinical team and infection control team as above.

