### Primary outcome

The primary outcome measure is the difference in the proportion of influenza-positive patients treated appropriately with NAI during their hospital stay (within 5 days of admission).

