#### Data collection, management and analysis

##### Data collection methods

Demographic and clinical data will be collected for all patients at enrolment from paper and electronic medical records including: age, sex, ethnicity, smoking status, vaccination status, comorbidities, medication use, symptoms, duration of illness prior to hospitalisation, observations (pulse rate, respiratory rate, blood pressure, oxygenation status), laboratory results, radiology results, antimicrobial and antiviral use prior to hospitalisation and provisional diagnosis. Data will be recorded on a standardised case report form (CRF) and transferred to a secure electronic database. Once patients have been discharged or after 30 days (whichever is soonest), outcome data will be collected retrospectively from electronic and physical case notes, electronic prescribing systems and laboratory and radiological results systems including: use of antivirals, duration of antivirals, time from assessment to antiviral use, use of antibiotics, duration of antibiotic use, use of side room facilities, time from assessment to isolation facility use, time to clinical stability, duration of supplementary oxygen use, duration of hospitalisation, complications including ICU and HDU admission, representation and readmission to hospital within 30 days, final diagnosis and mortality. The number of diagnostic tests and procedures performed will also be recorded and data will also be collected on the turnaround time of respiratory virus test results in each group. Patients withdrawn from the study will have no further data collected.

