### Primary outcome

The primary outcome (proportion of patients infected with influenza treated with NAIs) will be measured only in patients with confirmed influenza, that is, the intention-to-treat-infected (ITTI) population. Difference in proportions and unadjusted ORs will be used to compare the groups. The effect of group on the primary outcome will be further assessed using multiple logistic regression to control for the following covariates: age, sex, influenza vaccine status, receipt of antibiotics prior to admission, duration of illness, comorbidity, temperature, C reactive protein, severity of illness and clinical group.

Certain secondary outcome measures will be measured both in the entire cohort (ITT population) and in the influenza-infected cohort (the ITTI population) while others will only be measured in the ITTI population, as detailed in the outcome section. The intervention and control groups will be compared as per the primary outcome for equality of proportions for binary data and using t-tests and non-parametric equivalent tests for continuous data (eg, turnaround time) as appropriate.

In view of the clinical heterogeneity of patients infected with influenza, heterogeneity of effect among different clinical subgroups is anticipated a priori and therefore a preplanned subgroup analysis for key secondary outcome measures may be undertaken based on clinical group (exacerbation of asthma, exacerbation of COPD, pneumonia, ILI, non-pneumonic LRTI and ‘other’) and also based on receipt or otherwise of antiviral treatment (the receipt of NAIs within 5 days of admission). The interaction between clinical subgroups and allocation group will be assessed in the multiple regression models detailed above.

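### The optional subgroup analysis by NAI receipt within 5 days splits patients on a post-randomisation variable that POCT is meant to change, so arm comparisons within it are not randomised and are liable to mislead

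*Protocol article*

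**What the plan says.** The section on the primary outcome under Statistical methods says that "a preplanned subgroup analysis for key secondary outcome measures may be undertaken based on clinical group", and that the split is "also based on receipt or otherwise of antiviral treatment (the receipt of NAIs within 5 days of admission"). The reason given is the clinical heterogeneity of patients infected with influenza.

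Three other places bear on this split:

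- The primary outcome, in the list of outcomes, is the difference in "the proportion of influenza-positive patients treated appropriately with NAI during their hospital stay (within 5 days of admission"). The statistical section restates it more loosely: "The primary outcome (proportion of patients infected with influenza treated with NAIs) will be measured only in patients with confirmed influenza".
- The intervention acts directly on this variable: "In the event of influenza A or B being detected, clinical teams will be encouraged to offer treatment with NAIs as per national guidelines".
- The sample size section expects appropriate NAI use to rise from 65% to 85%, and cites 91% v 65% from the previous trial.

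On the interaction test, the plan says: "The interaction between clinical subgroups and allocation group will be assessed in the multiple regression models detailed above". That sentence names clinical subgroups only, so it is unclear whether it covers the NAI split. Nothing in the protocol calls the NAI split descriptive, and no method is given for dealing with selection after randomisation.

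**The concern.** A subgroup keeps the protection of randomisation only if allocation cannot affect who falls into it. Clinical group meets that condition if it is fixed at baseline. NAI receipt does not: it is a treatment decision taken after allocation, and the trial is designed so that the POCT arm takes it more often.

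Among treated patients, the POCT arm holds those who would have been treated anyway plus those treated because of the rapid result. The control arm holds only the former. Among untreated patients the mixing is reversed. The better POCT works on the primary outcome, the greater the imbalance.

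At stake are arm comparisons of outcomes such as length of stay, complications and mortality within these strata. They could show a benefit or a harm that does not exist, and the word preplanned would lend them credibility they have not earned.

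**Working it through.** **1. The plan's own figures.** Inputs from the Sample size section: about 100 influenza-positive patients per group (25% of 420 = 105), NAI use 65% v 85%, significance level 0.05 (taken as two-sided). Power = Φ{[|p1 − p2|√n − 1.96·√(2p̄(1 − p̄))] / √(p1q1 + p2q2)}.

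- 65% v 85%, n = 100: (2.000 − 1.200)/0.596 = 1.34, power 91.0% (92.3% at n = 105). Stated: 90%.
- 65% v 82%, n = 100: (1.700 − 1.223)/0.612 = 0.78, power 78.2% (80.1% at n = 105). Stated: 80%.

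Both stated powers reproduce within 2 points. The concern changes no sample size or power figure.

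**2. Who is in each stratum.** Assume that POCT only adds treatment, so no patient is treated under routine care but left untreated under POCT. At 65% v 85% the patient types are:

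- always treated: 0.65
- treated only if POCT is used: 0.85 − 0.65 = 0.20
- never treated: 1 − 0.85 = 0.15

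| Per 100 positives | Control | POCT |
|---|---|---|
| Treated | 65 (all always-treated) | 85 (65 always + 20 POCT-only) |
| Untreated | 35 (20 POCT-only + 15 never) | 15 (all never-treated) |

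The POCT-only type makes up 20/85 = 24% of treated POCT patients and 20/35 = 57% of untreated controls. At the earlier trial's 91%, the untreated stratum is 35 v 9.

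**3. The bias when nothing works.** Let rA, rC and rN be the outcome risks in the always-treated, POCT-only and never-treated types, with no effect of arm or NAI on the outcome. The apparent differences (POCT − control) are then:

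- treated: (0.20/0.85)(rC − rA)
- untreated: (0.20/0.35)(rN − rC)

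Illustration with assumed risks rA = 30%, rC = 15%, rN = 10%:

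- Both arms overall: 0.65×30 + 0.20×15 + 0.15×10 = 24.0%, so there is no difference.
- Treated: 0.235×(15 − 30) = −3.5 points (26.5% v 30.0%).
- Untreated: 0.571×(10 − 15) = −2.9 points (10.0% v 12.9%).

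This is a false benefit in both strata. With assumed risks of 20%, 10% and 20%, the treated difference is −2.4 points and the untreated difference is +5.7. Over the patterns tried at 65%/85% and 65%/91%, false differences ran from −5.7 to +2.9 points (treated) and from −3.7 to +7.4 points (untreated). They vanish only where the types being mixed have equal risk.

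**4. Effect on a test of length of stay.** Simulation with 100 positives per arm and no true effect: log stay = log 4 + 0.5×severity + N(0, 0.7), NAI receipt from a logistic model on severity, Mann–Whitney test, 2,000 trials per scenario. Control treatment was 65%, POCT 85% or 91%. The control log-odds slope was 0.5–1.5 per SD of severity, and the POCT slope ranged from zero to equal to control.

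- Whole ITTI population: rejects in about 5%, as it should.
- Treated stratum: rejects in roughly 6–27%. The low end has a slope of 0.5 in both arms. The high end has a control slope of 1.5 and no link to severity in the POCT arm.
- Untreated stratum: the false difference in stay runs from about −19% (equal slopes) to about +42% (no link in the POCT arm).

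**The case against.** The strongest reply is that little hangs on this analysis. It is optional, it concerns key secondary outcomes only, and the plan already compares the arms in the whole ITT and ITTI populations. That stands. A reader might infer that the primary result is compromised, but the documents do not support this: the primary comparison uses all confirmed influenza cases and does not condition on treatment.

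Second, the stratifier is not word for word the primary endpoint, which adds appropriateness and is limited to influenza-positive patients. That also stands: the match is near-complete, not exact.

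Third, the size of the bias rests on severity–treatment links that no document supplies. With equal slopes of 0.5 in both arms, rejection among the treated is only 5.7% (85% treated) or 7.0% (91%). Halving the effect of severity on stay to 0.25, with equal slopes of 0.5–1.0, gives 5–7.5%. No single figure or fixed direction can therefore be claimed. This does not rescue the comparison, because a bias that cannot be signed in advance is a reason not to preplan it.

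Two further inferences are tempting but unsupported:

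- **That the treated groups differ because treated POCT patients are nearly all influenza-positive.** The subgroup sentence is introduced by reference to infected patients, and within the ITTI population every patient in both arms is positive.
- **That clinical group is contaminated in the same way,** because outcome collection includes "representation and readmission to hospital within 30 days, final diagnosis and mortality". A provisional diagnosis is also recorded at enrolment, nothing says that the final diagnosis defines the group, and the choice of field is detail that an analysis plan normally settles.

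**Conclusion.** The concern holds in a limited form. As written, the plan lists as a subgroup factor a variable that is measured after randomisation, that the intervention is meant to change, and that is in substance the primary endpoint. The heterogeneity rationale fits clinical group but not this variable. An unseen analysis plan could relabel the split but could not make the arm comparison within it randomised.

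The stratum shares (24% and 57%) follow from the protocol's 65% and 85% plus the assumption that POCT only adds treatment. The 6–27% rejection range also needs the assumed severity model and is an illustration, not a forecast. It would be too strong to say that the analysis will mislead. It is liable to, by an amount that cannot be known in advance and, among the untreated, in a direction that cannot be known either. This should be fixed, but it does not threaten the trial's main conclusions.

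**What to change.** Remove NAI receipt from the preplanned subgroup list for the POCT v control comparison, and keep clinical group as the subgroup factor. If outcomes by NAI receipt are still wanted, there are two defensible routes:

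- present them as an exploratory, non-randomised association, and say so in the text; or
- prespecify a causal method, such as a principal stratum or mediation analysis, with its assumptions stated.

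The interaction sentence should then say which subgroups it covers. The cost is about a sentence of wording and no change to sample size. What is lost, or relabelled, is an optional exploratory arm comparison.

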### Monitoring

This trial was reviewed by the sponsor. On the basis of the very low risk of harms associated with the intervention in this non-Clinical Trial of an Investigational Medicinal Product (CTIMP) trial, no data monitoring committee or interim analysis is planned. A trial management committee will meet regularly and oversee the trial.

### Harms

The risks of respiratory tract sampling and additional blood tests being taken are minimal and where occurring are likely to be mild. No additional adverse events related to POCT for respiratory viruses are anticipated. However, active monitoring and reporting of severe adverse events will be undertaken. A serious adverse event (SAE) is any adverse event that:

Results in deathIs life threatening.Requires hospitalisation or prolongation of existing hospitalisation.Results in persistent or significant disability or incapacity.Consists of a congenital anomaly or birth defect.

Participants already admitted to AMU or are in ED but with a decision already made to admit are considered already hospitalised. However, an adverse event leading to prolongation of their existing hospitalisation will be counted as an SAE.

### Auditing

Regular monitoring by the sponsor will be performed according to ICH GCP. Data will be evaluated with regards to accuracy in relation to source documents and compliance with the protocol. Following written standard operating procedures, the monitors will verify that the clinical trial is conducted and data are generated, documented and reported in a manner that is compliant with the protocol, GCP and applicable regulatory requirements.

### Protocol amendments

There has been one amendment made to the protocol. This was the addition of Hampshire Hospitals NHS Foundation Trust as a potential site and removal of mention of ‘single centre’. The current protocol version is V.1.1, dated 23 November 2017. This amendment has been communicated to the investigators and the trial registries. The local study reference is RHM MED 1438.

### Confidentiality

All data will be anonymised to ensure patient confidentiality is protected. A unique study number will be used to identify participant data in the CRFs and database. SAEs will be reported in line with GCP and regulatory requirements. All study staff have been trained in GCP. Data will be kept securely and only the investigators and sponsor’s representative (monitor) have access to the data.

### Access to data

Full access to the dataset will be held by the principal investigator, coinvestigators and independent statistician only. The dataset may be made available to other parties on request.

### Dissemination policy

Authorship of this manuscript and those resulting from this protocol will follow the International Committee of Medical Journal Editors (ICMJE) recommendations and CONSORT statement where appropriate, and there are no plans to use professional writers. There is no intention to make the dataset publically available. Outside of the study team and regulators, the full protocol will only be made available at the discretion of the chief investigator. Multiple publications are expected to result from the data and samples collected, and these publications must acknowledge this trial and the study team as appropriate.

### Patient and public involvement

Discussion with members of the public and the results of questionnaire from hospitalised patients helped inform the design of this trial.

The emphasis on informing the patients, in addition to the clinical teams, of the POCT result is a direct result of our engagement with patients. Patients and the public will also be involved in the reporting of this research.

## Discussion

We hypothesise that the use of a routine molecular POC ‘test-and-treat’ strategy for influenza in adults hospitalised with acute respiratory illness will improve adherence to national guidelines for the management of influenza and may improve patient outcomes. We expect increased, timely detection of influenza and that this will lead to improved use of NAI treatment. Rapid and appropriate use of NAI treatment in influenza may also lead to decreased complication and mortality and may shorten length of stay in hospital. The rapid detection of viruses may improve isolation facility use within the NHS with subsequent reduction in nosocomial transmission of viruses and improvements in patient flow through acute areas. The use of a POCT for respiratory viruses may also identify patients where unnecessary antibiotic use can be safely discontinued, promoting antibiotic stewardship and reducing antimicrobial resistance.
